### Objectives

#### Primary objective 1

To determine whether complementing UC with financial incentives for good treatment adherence is superior to UC alone in reducing HbA1c at 6 months.

#### Primary objective 2

To determine whether incentivising intermediate health outcomes (self-monitored blood glucose levels within acceptable range) is superior to incentivising intermediate processes (blood glucose testing, physical activity, and medication adherence) in reducing HbA1c at 6 months.

#### Secondary objective 1

To assess whether complementing UC with financial incentives for good treatment adherence is superior to UC alone in improving treatment adherence as measured by the proportion of glucose tests and medications taken as prescribed and average number of daily steps taken between baseline and 6 months.

#### Secondary objective 2

To assess whether incentivising health outcomes is superior to incentivising intermediate processes in improving treatment adherence as measured by the proportion of glucose tests and medications taken as prescribed and average number of daily steps between taken baseline and 6 months.

#### Secondary objective 3

To assess which intervention (i.e. incentivising health outcomes or processes) has the most favourable incremental cost-effectiveness ratio (ICER) for HbA1c reductions between baseline and 6 months compared to UC alone.

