#### Secondary outcomes

*Mean number of blood glucose days at month 6*. Up to three non-consecutive testing days during the last week of the intervention will be counted. This outcome corresponds to UC’s recommendations and to one of the goals that is incentivised in the process incentive arm
*Mean number of glucose readings that fall between 4 and 7 mmol/L at month 6*. This outcome is consistent with UC’s recommendations for blood glucose testing before meals. Consistent with the outcome incentive arm’s goal, only the first reading recorded on a maximum of three non-consecutive days will be taken into consideration during the last week of the intervention
*Mean number of medication-adherent days at month 6*. Medication-adherent days are defined as days where all medication doses were taken during pre-defined time windows as verified by the medication tracker. The number of medication-adherent days during the last week of the intervention will be calculated for each participant. This outcome corresponds to UC’s recommendation and to one of the goals that is incentivised in the process incentive arm
*Mean number of physically active days at month 6*. The number of days where the pedometer records at least 8000 steps during the last week of the intervention will be calculated for each participant. This outcome corresponds to UC’s recommendations and to one of the goals that is incentivised in the incentives arm.
*Mean cost of financial incentives at month 6.* This outcome will be calculated as the total contingent financial incentives earned by process incentive and outcome incentive arm participants during the last week of the intervention. This outcome will be used as part of the cost-effectiveness analysis
*Mean time taken by the intervention at month 6.* This outcome will be calculated as the total number of minutes spent by the CRC on adherence calculation and payment of financial incentives for process incentive and outcome incentive arms participants during the month-6 assessment. This outcome will be used as part of the cost-effectiveness analysis

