#### Secondary analyses

The number of blood glucose testing days, glucose readings within acceptable range, medication-adherent days, and physically active days at month 6 will be linearly regressed on binary variables indicating the intervention arms and on the same baseline characteristics as for the primary analysis. If the interventions show statistically significant improvements in HbA1c levels, we will conduct a cost-effectiveness analysis for both intervention arms. The perspective of the cost-effectiveness analysis will be that of the health system. Effectiveness will be measured by the primary outcome and costs will include the average financial incentives paid, labour costs associated to the administration of the incentives, and the cost of devices. The incremental cost-effectiveness ratio between each intervention and UC will be calculated and compared to those of other interventions aiming at reducing HbA1c levels.

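### The incentive-cost and staff-time outcomes cover one week of 24 and one payment visit of two, which does not match the baseline-to-6-month cost-effectiveness ratio they are meant to feed.

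*Protocol article*

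**What the plan says.** All references are to the protocol article.

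- **Objectives, Secondary objective 3** asks which intervention has the "most favourable incremental cost-effectiveness ratio (ICER) for HbA1c reductions between baseline and 6 months compared to UC alone". No condition is attached.
- **Secondary outcomes** defines the mean cost of incentives as "the total contingent financial incentives earned by process incentive and outcome incentive arm participants during the last week of the intervention". Staff time is the coordinator's minutes on adherence calculation and payment "for process incentive and outcome incentive arms participants during the month-6 assessment". Of each it says: "This outcome will be used as part of the cost-effectiveness analysis".
- **Secondary analyses** describes the analysis itself: "costs will include the average financial incentives paid, labour costs associated to the administration of the incentives, and the cost of devices". No time window is given. The ratios are then compared with those of other interventions that lower HbA1c. The section also sets a precondition: "If the interventions show statistically significant improvements in HbA1c levels, we will conduct a cost-effectiveness analysis for both intervention arms". It does not say which contrast or significance level counts.
- **Arm 2** and **Arm 3** (and Table 1) let participants earn up to SGD14 a week, SGD336 over two 12-week periods.
- **Participant timeline and study arms** has adherence and payments worked out at months 3 and 6. **Data collection** records payments made and coordinator time at both visits.

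**The concern.** A cost-effectiveness ratio is meaningful only if cost and effect cover the same period. Here the effect is the HbA1c change over the whole 6 months, while the two cost inputs given an explicit window are a final-week snapshot and a single visit. An analyst who follows the outcome definitions literally sets a fraction of the cost against the full effect.

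The error would run one way, towards making incentives look cheap, and the ratio is to be set beside those of other interventions. Objective 3 also ranks the process and outcome arms. A last-week figure could distort that ranking if earnings move differently over time in the two arms.

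The significance condition is a separate, smaller mismatch, because it makes an unconditional objective depend on a test result.

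**Working it through.** **1. Reproduce the plan's maximum.** Process arm: 3.50 + 7 × 0.50 + 7 × 1.00 = SGD14 a week; 14 × 24 = SGD336. Outcome arm: 14 × 24 = SGD336. Both agree with Table 1.

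**2. Coverage of the defined inputs.** Incentives: 14/336 = 1/24 = 4.2%, a 24-fold gap on this component if weekly earnings are level and the one-week figure enters unscaled. Staff time: 1 of 2 payment visits, about half if the visits take equal time. The article gives no visit durations.

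**3. Is multiplying by 24 a safe repair?** The article gives no earnings trend, so two linear drifts in the share of the weekly maximum are assumed. Both average 55%, so both total 336 × 0.55 = SGD184.8.

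| Assumed drift | Last week | Total ÷ last week | Last week × 24 | Scaled ÷ true |
|---|---|---|---|---|
| 80% falling to 30% | 14 × 0.30 = SGD4.2 | 44 | SGD100.8 | 0.55 |
| 30% rising to 80% | 14 × 0.80 = SGD11.2 | 16.5 | SGD268.8 | 1.45 |

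Two arms with identical total cost would look 11.2/4.2 = 2.7-fold apart.

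**4. Effect on the whole ratio.** The HbA1c effect is the same in both versions and cancels, so the understatement is full cost ÷ cost as defined. Assumptions: SGD10 labour per visit, level earnings, and a range of device costs charged to the intervention.

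| Share of maximum earned | Device cost charged | Full cost | Cost as defined | Understatement |
|---|---|---|---|---|
| 100% | 0 | 336 + 20 = 356 | 14 + 10 = 24 | 14.8-fold |
| 50% | 0 | 168 + 20 = 188 | 7 + 10 = 17 | 11.1-fold |
| 100% | SGD100 | 456 | 124 | 3.7-fold |
| 50% | SGD100 | 288 | 117 | 2.5-fold |
| 100% | SGD200 | 556 | 224 | 2.5-fold |
| 50% | SGD200 | 388 | 217 | 1.8-fold |

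The pedometer and medication tracker go to all three arms, so a zero incremental device cost is plausible, but the article does not settle this.

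**5. Chance that the significance condition suppresses the ratio.** Inputs from Sample size: SD 2, effect 1 point, significance level 2.5%, 60 and 90 per arm with about 20% attrition, leaving 48 usual care and 72 + 72 = 144 pooled.

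The stated sizes reproduce with a two-sided test. 2 × 2² × (2.241 + 0.842)² / 1² = 76.0, against 76 stated. With 152 fixed, 1/(1/38.02 − 1/152) = 50.7, giving the stated 51.

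Pooled contrast: SE = 2 × √(1/48 + 1/144) = 0.333. At a true 1-point effect, z = 3.00 and power = Φ(3.00 − 2.24) = 77.6%, so no ratio is produced about 22% of the time. For one arm against usual care (48 vs 72), power is 67%. At 5% two-sided the figures are 85% pooled and 77% for one arm. Across these readings the chance of no ratio is roughly 15% to 33%.

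**The case against.** The strongest reply is that the outcome definitions do not bind the analysis. They say only that each outcome forms part of it. The section that specifies the analysis refers to average incentives paid, with no last-week limit, and payments and minutes are recorded at both visits. On that reading the full-period ratio is what was meant. This stands to the extent that a correct ratio can be computed from the planned data. It does not remove the mismatch, because the only explicit windows in the article are the narrow ones and those outcomes are expressly assigned to this analysis.

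A reader might infer that the published ratio must be wrong by a factor of 24. The documents do not support that. The factor applies to one component, at level earnings, used unscaled; labour and devices dilute it. Nor do they show that the two arms would be ranked wrongly, since no earnings trend is given.

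A reader might also infer that the ratio will probably never be produced. At the 0.45-point reduction cited in the Background, pooled power on the inputs above is about 19%. But that figure is a non-significant estimate from another population, not the design effect. SD 2 is unadjusted, whereas the primary model adjusts for baseline HbA1c and other covariates, which would raise power. The contrast and level behind the condition are also assumed here.

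Finally, making a secondary analysis depend on the primary result is openly pre-specified. It is not an error of fact, though it narrows objective 3. At the design effect, selecting on significance inflates the estimate only modestly: the mean z given significance is about 3.39 against a true 3.00, or 13%.

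**Conclusion.** The point holds as a mismatch of definitions. The cost inputs named under Secondary outcomes do not cover the period that Secondary objective 3 requires, and Secondary analyses gives no window that would settle it. If they are used as defined, cost is understated: by 24-fold on incentives at level earnings, about 2-fold on staff time if the visits are alike, and by 1.8- to 14.8-fold overall on the illustrative inputs. No single multiple can be claimed, because labour rates, device charging and earnings over time are not in the article.

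The significance condition is secondary. It would leave objective 3 unanswered about 22% of the time at the design effect (pooled contrast, unadjusted SD 2, two-sided 2.5%), and more often at smaller effects.

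The primary outcome and its analysis are unaffected.

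**What to change.** - Redefine the incentive-cost input as all contingent incentives paid from baseline to month 6, that is, the month-3 plus month-6 payments for each participant.
- Redefine the staff-time input as coordinator minutes on adherence calculation and payment summed over both visits.
- Keep last-week earnings as a descriptive outcome, without the statement that it feeds the cost-effectiveness analysis. Do not scale it up as a substitute.
- State the baseline-to-6-month window in Secondary analyses, and say whether devices issued to all arms count as an incremental cost.
- Remove the significance condition and report each ratio against usual care with its uncertainty whatever the HbA1c p-value. The method for the uncertainty can be left to the analysis plan.

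The cost is wording and a modest amount of analysis. Payments and minutes at both visits are already to be recorded, so no new data collection is needed. Recruitment was still under way at the article's status date, so the change could be made before the final analysis.

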#### Explanatory outcomes

*Mean change from baseline in glycated haemoglobin HbA1c at months 12 and 18*

*Proportion of participants whose oral medication was titrated up at months 6, 12 and 18*

*Proportion of participants who switched to insulin therapy at months 6, 12 and 18*

*Mean change from baseline in EQ-5D-5L* [21] *score at month 6* as a measure of functional health status. This scale has been validated in people with type-2 diabetes [22]. In Singapore, both the English and Mandarin versions have been validated in people with cancer [23]
*Mean change from baseline in Brief Illness Perception Questionnaire* [24] *(BIPQ) score at month 6*. This scale has been validated in English for multiple health conditions including diabetes [25]. The Mandarin version has been validated in Taiwan in people with coronary heart disease [26]
*Mean change from baseline in Self-Monitoring of Blood Glucose* [27] *(SMBG) score at month 6*. This scale has been validated in English in people with type-2 diabetes but has yet to be validated in Mandarin and in Singapore
*Mean change from baseline in general and specific scores of the* Beliefs about Medication Questionnaire [28] *(BMQ) at month 6*. The English version of the scale has been validated for several chronic diseases including diabetes [29] while the Mandarin version has been validated in other settings such as after mechanical heart-valve replacement [30] and depression [31]. Validity in Singapore has not been established for this scale
*Mean change from baseline in the exercise subscale of the Diabetes Self-Care Activities* [32] *(DSCA) at month 6.* The English version of the scale has been pretested for acceptability and comprehensibility in a study involving people with type-2 diabetes [32] but has neither been pretested in Mandarin nor in Singapore

### Sample size

A key parameter is the variability in post-intervention HbA1c levels. To assess this, we have used data from a pilot intervention aimed at improving diabetes outcomes through a comprehensive educational and management programme (that did not include financial incentives). Among 54 participants with suboptimally controlled diabetes, we found that the standard deviation in participant HbA1c levels was 1.29 at baseline and 1.99 after a 3-month intervention. Based on this data, we decided to use a standard deviation of 2 for the variability in post-intervention HbA1c levels to calculate the sample size for this trial.

We have first computed the size of the intervention arms that is required for testing whether there is a statistical difference between post-intervention HbA1c levels between the outcome and process incentive arms (primary objective 2). After applying a Bonferroni correction by dividing the test’s significance level by 2 (which is the number of primary hypotheses to test in this trial), we found that 76 participants per intervention arm are necessary to detect mean differences in HbA1c levels of 1% between these study arms (with significance level of 5/2 = 2.5% and 80% power). Given the resulting cumulated sample size for the intervention arms of 76 + 76 = 152, we then computed the size required for the UC arm to test the overall effect of financial incentives (primary objective 1) with the same effect size, significance level, and power. This computation yielded a sample size of 51 for the UC arm. After accounting for approximately 20% attrition in each study arm, we set the final sample size at 60 for the UC arm and 90 for each intervention arm, for a grand total of 240 participants.

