The first primary objective of this trial is to determine whether adding financial incentives to usual care (UC) can improve HbA1c levels among people with suboptimally controlled type-2 diabetes in the primary-care setting. The second primary objective is to determine whether financial incentives should be directed at processes (adherence to blood glucose testing, medication, and daily physical activity) or at achieving intermediary health outcomes (self-monitored blood glucose within acceptable range). This trial will provide novel head-to-head evidence on which strategy works best. In addition, the trial will assess the effect of financial incentives on treatment adherence and whether such incentives constitute cost-effective intervention strategies for diabetes management. Finally, explanatory analysis will aim at determining whether patient perception about diabetes management is altered by the interventions, uncovering factors that might moderate the effect of financial incentives, and identifying socioeconomic groups that may benefit more from the interventions.

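### Holm's step-down test would give the two primary hypotheses the same 5% familywise error as the plain Bonferroni split, with equal or higher power and no extra patients (optional efficiency gain, not an error)

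*Protocol article*

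**What the plan says.** The protocol article names two primary objectives: whether adding incentives to usual care lowers HbA1c, and, in its Rationale, "The second primary objective is to determine whether financial incentives should be directed at processes" or at intermediary health outcomes.

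Multiplicity is handled in the Sample size section. The level is set "After applying a Bonferroni correction by dividing" it by two, "which is the number of primary hypotheses to test in this trial". The process-versus-outcome comparison is sized first: "76 participants per intervention arm are necessary to detect mean differences in HbA1c levels of 1% between these study arms". The error rate and power used for that step are given in brackets: "with significance level of 5/2 = 2.5% and 80% power". The usual care arm is then sized against the 152 pooled incentive participants "with the same effect size, significance level, and power", which gives 51. On variability, "we decided to use a standard deviation of 2 for the variability in post-intervention HbA1c levels". Enrolment is set at 60, 90 and 90 to allow for about 20% attrition.

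The Primary analysis section describes the regression model and names no multiplicity procedure. The split therefore appears only where the trial is sized.

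**The concern.** Under a fixed split, each primary hypothesis is judged at 2.5% whatever happens to the other. If one objective succeeds and the other gives a p-value between 0.025 and 0.05, the second is declared non-significant. Holm's procedure would declare it significant at the same familywise error. It tests the smaller p-value at 2.5% and, if that succeeds, tests the other at 5%.

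This matters because the trial sets out to answer both questions: whether incentives work, and which kind works better. The chance of answering both is where the two procedures differ most. Significance also has a downstream use, since the Secondary analyses section makes the cost-effectiveness analysis conditional on significant HbA1c improvement.

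**Working it through.** **Inputs** (Sample size section): difference 1 point for both contrasts; SD 2; 2.5% per test; 80% power; evaluable sizes 76 and 76 (incentive arms) and 51 (usual care); enrolled 90, 90 and 60. Sidedness is not stated. Two-sided 2.5% reproduces 76, whereas one-sided 2.5% gives 63, so two-sided is taken.

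**Reproducing the plan** (normal approximation; z-values 2.2414 and 0.8416, sum 3.083)
- Incentive arms: n = 2 × 2² × 3.083² / 1² = 76.04. The plan states 76, where power is 79.98%.
- Usual care: 1/n = (1/(2 × 3.083))² − 1/152 = 0.02630 − 0.00658 = 0.01972, so n = 50.7. The plan states 51, where power is 80.2%.

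**Error control under Holm.** If both nulls are true, a false rejection needs the smaller p-value to be at or below 2.5%, which has probability at most 2 × 2.5% = 5% under any dependence (4.94% if the contrasts are independent, the same as Bonferroni). If one null is true, it is never tested above 5%.

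**Power.** Write a for power at 2.5% and b for power at 5%. With equal incentive arms the two contrasts are orthogonal and are treated as independent. This is used only to size the gain.
- Holm, objective 1: a₁ + (b₁ − a₁) × a₂, and likewise for objective 2.
- Both rejected: a₁a₂ under Bonferroni; b₁b₂ − (b₁ − a₁)(b₂ − a₂) under Holm.
- At least one rejected: 1 − (1 − a₁)(1 − a₂) under either.

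*Planned evaluable sizes, both effects 1 point:* a₁ = 0.8019, b₁ = 0.8707, a₂ = 0.7998, b₂ = 0.8691.
- Objective 1: 0.8019 + 0.0688 × 0.7998 = 0.857.
- Objective 2: 0.7998 + 0.0693 × 0.8019 = 0.855.
- Both: 0.8019 × 0.7998 = 0.641 (Bonferroni); 0.8707 × 0.8691 − 0.0688 × 0.0693 = 0.752 (Holm).

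*After 20% loss from 60/90/90, leaving 48/72/72:* SE = 2√(2/72) = 0.333 for objective 2 and 2√(1/48 + 1/144) = 0.333 for objective 1. The ratio of difference to SE is 3, so a = 0.776 and b = 0.851 for each.
- Per objective: 0.776 + 0.0748 × 0.776 = 0.834.
- Both: 0.602 (Bonferroni); 0.718 (Holm).

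Results in %, sizes as usual care/process/outcome, true contrasts in points of HbA1c (objective 1, objective 2):

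| Sizes | True contrasts | Bonferroni, obj. 1 / 2 | Holm, obj. 1 / 2 | Both: Bonferroni → Holm | At least one, either method |
|---|---|---|---|---|---|
| 51/76/76 | 1, 1 | 80.2 / 80.0 | 85.7 / 85.5 | 64.1 → 75.2 | 96.0 |
| 48/72/72 | 1, 1 | 77.6 / 77.6 | 83.4 / 83.4 | 60.2 → 71.8 | 95.0 |
| 51/76/76 | 1, 0.5 | 80.2 / 24.2 | 81.9 / 31.9 | 19.4 → 28.8 | 85.0 |
| 51/76/76 | 0.5, 0.5 | 24.3 / 24.2 | 26.6 / 26.5 | 5.9 → 10.5 | 42.6 |

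If only one effect is real (1 point, the other null), power for the real one goes from 80.2% to 80.4% (objective 1) or from 80.0% to 80.2% (objective 2) at the planned sizes, and from 77.6% to 77.8% after 20% loss.

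**The case against.** The strongest reply is that nothing in the document is wrong. Bonferroni is a valid correction for two hypotheses, and the trial was sized to deliver 80% at 2.5%. A reader might infer that the split throws away power the trial was counting on. The documents do not support that, because 76 and 51 already carry the cost of the split. This part of the reply stands.

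Three further points stand in part.

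- **The gain depends on the scenario.** The largest figures need both contrasts to be 1 point. With equal incentive arms, and outcome incentives the better, that means outcome incentives beat usual care by 1.5 points and process incentives by 0.5. The Rationale cites pooled reductions of 0.20 to 0.57 for other interventions and a non-significant 0.45 for an incentive study. Smaller effects shrink the gain but do not reverse it. Even so, 1 point on both is the scenario for which the plan itself is sized.
- **The thin margin has another cause.** A reader might infer that Holm repairs the drop below 80%. The drop arises because 60 and 90 absorb losses of only 1 − 51/60 = 15.0% and 1 − 76/90 = 15.6%, not 20%. If only one effect is real, Holm moves 77.6% to just 77.8%.
- **Bonferroni has an advantage of its own.** Its 97.5% intervals always agree with its tests. Under Holm, a contrast declared significant at the second step with p between 0.025 and 0.05 has a 97.5% interval that includes zero.

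A reader might also infer that the final tests are irrevocably fixed at 2.5%. The article states that level for sizing only, and its analysis section neither adopts nor excludes a step-down test. The point therefore rests on the method that the article names, not on an omission.

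**Conclusion.** The point holds as an optional efficiency improvement; the plan contains no error here. Holm keeps familywise error at 5% under any dependence and is never less powerful. On the plan's own inputs it adds about 5.5 points of power per objective and 11 points for winning both at the planned evaluable sizes, and about 6 and 12 points after a full 20% loss. The gain per objective falls to a little over 2 points with two 0.5-point effects and to about 0.2 point with a single real effect. The probability of rejecting at least one hypothesis does not change.

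The figures assume two-sided tests, the normal approximation, SD 2, independent contrasts and no variance reduction from baseline HbA1c or the other covariates. Those assumptions affect the size of the gain, but Holm's error control does not depend on the contrasts being independent.

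**What to change.** In a dated amendment or in the analysis plan, state that the two primary contrasts (pooled incentives versus usual care, outcome versus process) are tested by Holm's procedure at a two-sided familywise 5%: the smaller p-value against 2.5% and, if significant, the other against 5%. Keep 2.5% as the conservative sizing basis. Report 97.5% confidence intervals for both contrasts, and note that they may not match every Holm decision.

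The sentence should be in place before any by-arm HbA1c result is seen. Unblinding is not a usable marker here: allocation is open, and the Data management and monitoring section plans HbA1c assessments at 80 and 160 completers. Trial status reports 140 enrolled at 31 May 2017 and does not say whether the first assessment had taken place, so this should be checked and recorded. If by-arm results had already been seen, relaxing a published level would carry a credibility cost, and keeping Bonferroni would be reasonable.

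Otherwise the cost is one sentence, with no extra patients, no extra data and no change to the sample size.

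### The enrolled sizes of 90 and 60 cover about 15% attrition, not the stated 20%; at 20% the planned power is about 78%, not 80%

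*Protocol article*

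**What the plan says.** All the relevant statements stand in the Sample size section of the protocol article.

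- Variability: "we decided to use a standard deviation of 2 for the variability in post-intervention HbA1c levels".
- Primary objective 2 (outcome against process incentives): "76 participants per intervention arm are necessary to detect mean differences in HbA1c levels of 1% between these study arms", at a Bonferroni-corrected level, "with significance level of 5/2 = 2.5% and 80% power".
- Primary objective 1 (both incentive arms pooled, 152 participants, against UC): sized "with the same effect size, significance level, and power". The result: "This computation yielded a sample size of 51 for the UC arm".
- Enrolment: "After accounting for approximately 20% attrition in each study arm, we set the final sample size at 60 for the UC arm", with 90 in each incentive arm, for a total of 240. This matches the 2:3:3 allocation given under Trial design.

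**The concern.** The section treats 76 and 51 as the numbers needed for 80% power and presents 90 and 60 as those numbers after an allowance of about 20% for attrition. If a fraction d of those enrolled is lost, the enrolled number must be the evaluable number divided by (1 − d). The step from 76 to 90 is an uplift of 18.4% (90/76 = 1.184), and the step from 51 to 60 is 17.6% (60/51 = 1.176). For a 20% loss the uplift must be 25% (1/0.8 = 1.25).

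Both primary contrasts are affected. The section is the public justification for 240 participants and is likely to be carried into the results paper. If a primary contrast turns out not significant, readers would interpret it against a power that the calculation does not support at the attrition rate it names.

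**Working it through.** **Inputs (Sample size section):** standard deviation (SD) 2; difference δ = 1 HbA1c percentage point; significance level 0.025 per primary hypothesis; power 0.80; attrition 20% in each arm; enrolled 90, 90 and 60. Sidedness is not stated. I take the tests as two-sided because that reproduces 76, whereas one-sided 0.025 would give 63. The normal quantiles are 2.2414 (two-sided 2.5%) and 0.8416 (80% power). Their sum is 3.0830, and its square is 9.505.

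**Step 1: reproduce the evaluable sizes.**

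- Objective 2, per arm: n = 2 × SD² × 9.505 / δ² = 2 × 4 × 9.505 = 76.04. The plan states 76. Strict rounding up gives 77, which is immaterial.
- Objective 1, UC against 152: n = 1 / [1/(4 × 9.505) − 1/152] = 50.7, so 51. The plan states 51.

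**Step 2: inflate for 20% attrition.**

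| Arm | Evaluable | Divided by 0.8 | Multiplied by 1.2 | Enrolled in plan |
|---|---|---|---|---|
| Each incentive arm | 76 | 95 | 91.2 | 90 |
| UC | 51 | 63.75, so 64 | 61.2 | 60 |

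The correct total is 95 + 95 + 64 = 254, or 256 as 64/96/96 if 2:3:3 is kept exactly. The planned 90 and 60 lie close to the products with 1.2, which is consistent with multiplying by 1 + d and rounding down to the allocation ratio. The article does not show its formula, so that origin is only a conjecture.

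**Step 3: what the planned sizes leave.**

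- At 20% loss: 90 × 0.8 = 72, against 76 needed; 60 × 0.8 = 48, against 51 needed.
- Loss that can be absorbed: 1 − 76/90 = 15.6% in each incentive arm; 1 − 51/60 = 15.0% in UC.

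**Step 4: power at 20% loss.**

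- Objective 2, 72 against 72: standard error (SE) = 2 × √(1/72 + 1/72) = 0.333.
- Objective 1, 144 against 48: SE = 2 × √(1/144 + 1/48) = 0.333, the same value.
- In both cases power = Φ(1/0.333 − 2.2414) = Φ(0.759) = 77.6%. The noncentral t distribution gives 76.8% for objective 2 and 77.0% for objective 1.
- Difference detectable with 80% power: 3.0830 × 0.333 = 1.03 points.

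**Step 5: other attrition rates** (normal approximation, same for both contrasts).

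| Attrition | Power |
|---|---|
| 0% | 86.7% |
| 15% | 80.3% |
| 17.5% | 79.0% |
| 20% | 77.6% |
| 25% | 74.6% |

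**Check of the corrected sizes.** With 95/95/64 enrolled and 20% lost, power is 80.0% for objective 2 and 80.3% for objective 1.

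**The case against.** The strongest reply is that the calculation is not the analysis. It compares post-intervention HbA1c without adjustment, whereas the Primary analysis section regresses change in HbA1c on arm, baseline HbA1c and other baseline characteristics in order to gain efficiency. If the baseline to month-6 correlation is ρ, adjustment multiplies the residual SD by √(1 − ρ²). At 72/72/48 the power is back to 80% once √(1 − ρ²) = 1/1.0277, that is, at ρ of about 0.23. The article gives no correlation, so the following is an assumption with a range: ρ = 0.2 gives 79.4%, ρ = 0.3 gives 81.7% and ρ = 0.5 gives 88.9%. This stands as far as it goes: the trial may well have 80% power in its actual analysis. It does not rescue the stated justification, which neither claims nor quantifies such a gain.

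Other points carry less weight.

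- Attrition is described as approximate. That covers rounding, but 15% is not about 20%, and power is already below 80% at 17.5%.
- Multiple imputation keeps everyone randomised in the analysis. It does not supply month-6 measurements that were never taken, and the plan itself judged an attrition allowance necessary.
- Rounding to 2:3:3 does not explain the gap, since 64/96/96 has the same ratio.
- The shortfall is small beside the uncertainty in an SD taken from 54 pilot participants. That is fair and bears on how much weight the point deserves. It does not make the stated figure right.

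**Conclusion.** The concern holds. On the plan's own inputs, 90 and 60 do not deliver the stated 80% power at the stated 20% attrition: power is 77.6% for each primary contrast, 2.4 percentage points short, and the attrition actually covered is 15.0% to 15.6%. Full coverage would need 14 more participants, or 16 to keep the ratio exact.

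The result rests on two-sided tests at 2.5%, an SD of 2, a difference of 1 point and an unadjusted comparison, all as the plan's calculation uses or implies them. It does not show that the adjusted primary analysis will be underpowered. It shows that the published justification is wrong as written. The error is modest, affects both primary objectives and should be corrected.

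**What to change.** Keep 240 and make the sentence agree with the numbers. Either version will do:

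- state that 90, 90 and 60 allow for about 15% attrition in each arm; or
- keep 20% attrition and state that it leaves 72, 72 and 48 evaluable participants, with about 78% power for each primary contrast under the unadjusted calculation.

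If the sponsor wants credit for baseline adjustment, the assumed correlation should be stated and the power recalculated with it.

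The cost is one sentence and a slightly less favourable figure, with no change to procedures or analysis and no extra participants. Enrolling 256 (64/96/96) would instead make the present sentence true. The Trial status section reports recruitment still under way, with 140 enrolled by 31 May 2017, but the size of the shortfall does not require this.
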